## **7.5 Pregnancy and Contraception**

Ambroxol is not recommended during pregnancy as it crosses the placental barrier and when breast feeding as ambroxol is excreted in breast milk and participants that are pregnant or breastfeeding will be excluded from the study.

All male and female participants of child bearing potential must agree with their partners to use double-barrier birth control or abstinence whilst participating in the study and for 2 weeks following the last dose of the study drug as specified in the inclusion and exclusion criteria.

In addition, regular pregnancy testing will be performed for female of potential child-bearing status during the study if applicable.

## **8. Trial Procedures**

### **8.1 Recruitment**

Potential participants will be approached by their treating clinician (who in the case of this study may also be the CI/PI, Co-Investigator or PI-delegated clinician) during routine standard of care outpatient appointments at the RFH or the NHNN. Potential participants will be given a participant information sheet (PIS) and the opportunity to ask questions before deciding whether or not to take part.

### **8.2 Participant Identification Centres (PIC)**

The RFH will be the PIC and will refer all potential participants to NHNN at UCLH. The CI/PI, Co-Investigator and PI-delegated clinicians at the RFH have UCLH honorary contracts.

### **8.3 Informed Consent Process**

It is the responsibility of the CI/PI Investigator, or a PI-delegated clinician to obtain written informed consent from each participant prior to participation in the trial, following adequate explanation of the aims, methods, anticipated benefits and potential hazards of the trial.

The person taking consent will be GCP trained, suitably qualified and experienced, and will have been delegated this duty by the CI/ PI on the Staff Signature and Delegation of Tasks.

**“Adequate time”** must be given for consideration by the participant before taking part. Consent will be sought at least 24 hours after being given the study documentation. It must be recorded in the medical notes when the PIS have been given to the participant.

A copy of the signed informed consent form will be given to the participant. The original signed form will be retained in the trial file at site and a copy placed in the medical notes. Participants are under no obligation to enter the trial and can withdraw at any time during the trial without providing a reason.

The PIS and consent form will be reviewed and updated if necessary throughout the trial (e.g. where new safety information becomes available) and participants will be re-consented as appropriate.

#### **8.4 Re-screening of Participant**

Participant may repeat the screening procedures once to be eligible for the study if they have:

- Used anticoagulant therapy apixaban (Eliquis), dabigatran (Pradaxa) rivaroxaban (Xarelto) and Warfarin within 30 days prior to Screening Visit 2 (rescreening may be performed 14 days or more after discontinuation of anticoagulant therapy).
- An abnormal test value may normalise, in the opinion of the Investigator (rescreening may be performed once test values is within normal range).

#### **8.5 Informed consent for Genotyping/disclosure of previously held genotyping**

The study will recruit an equal number of *GBA*-positive and *GBA*-negative participants. Participants will be genotyped for *GBA* and *LRRK2* (a relatively common genetic risk factor for PD) at screening visit 1. All participants who have not undertaken genotyping in an NHS certified laboratory will be genotyped. The genotyping for *LRRK2* is essential to prevent the confounding effect of this genetic form of Parkinson's disease on our results.

All participants will be asked whether they wish to be told the results of their genotyping and counselled accordingly as part of standard of care procedures by researchers with referral onto local genetic counselling services if required.

#### **8.6 Study Procedure Assessments**

The CI/PI or PI-delegated member of the research team will conduct each assessment highlighted in Appendix 1, schedule of events.

The following clinical and non-clinical assessments will be conducted during the study: informed consent, medical history, physical examination, neurological examination, movement disorder society (MDS-sponsored) revision of the Unified Parkinson's Disease Rating Scale United Parkinson Disease's Rating Scale (MDS-UPDRS), Montreal Cognitive Assessment (MoCA), non-motor symptom (NMS) questionnaire, non-motor symptom scale (NMSS), weight, height, electrocardiogram (ECG), vital signs, lumbar puncture, concomitant review, adverse events review, dispensing and collecting IMP packaging, urine collection, dosing (day 1 to 186), IMP compliance and dosing instructions, blood and CSF biomarkers and routine blood samples.

##### **8.6.1 Unified Parkinson Disease Rating Scale (MDS-UPDRS)**

The MDS-UPDRS is made up of the following:

Part I: evaluation of mentation, behaviour, and mood.

Part II: self-evaluation of the activities of daily life (ADLs) including speech, swallowing, handwriting, dressing, hygiene, falling, salivating, turning in bed, walking, and cutting food.

Part III: clinician-scored monitored motor evaluation.

Part IV: complications of therapy.

Part V: Hoehn and Yahr staging of severity of Parkinson disease.

Part VI: Schwab and England ADL scale

The scales provide an impartial measure of disease progression in established PD and are validated as such (Wenning et al., 2004). The assessment is evaluated by interview and clinical observation. The duration is 30-60 minutes and will be administered in the morning of each study visit.

#### **8.6.1.1 MDS-UPDRS Restrictions**

On screening visit 2, visit 3 (day 1), visit 5 (day 93), visit 6 (day 186) and visit 7 (day 279), participants must refrain from taking their standard of care PD medication (standard of care procedure) until they have undertaken the UPDRS assessment in the morning, and will be advised accordingly by the PI or PI-delegated member of the research team when to administer their standard of care medication during the study visits which will be also be highlighted in the participant dosing instruction booklet.

#### **8.6.2 Vital Signs**

Vital signs include the measurements of a blood pressure (BP), pulse rate (PR), respiration rate (RR) and temperature (T) must be performed as single reads. Prior to the blood pressure assessment the participant should remain rested in a seated position for 10 minutes. The BP measurement should be recorded whilst the participant is in a seated position. If results are abnormal, repeat testing can be performed and assessed by the CI/PI or PI-delegated clinician.

#### **8.6.3 Montreal Cognitive Assessment (MoCA)**

The MoCA is a screening test for cognitive impairment that spans the visuospatial/executive, naming, memory, attention, language, abstraction, delayed recall and orientation domains will be recorded at selected study visits. It is a multi-domain cognitive battery validated in established PD and the score ranges from 0 to 30 points (Hoops et al., 2009). The duration is 10-20 minutes and must be administered preferably in the morning of selected study visits.

#### **8.6.4 Parkinson Disease Non-Motor Symptom Scale (NMSS)**

The NMSS is a validated 30 question scale designed to detect the non-motor features of Parkinson's disease.(Martinez-Martin et al., 2015). The duration of the scale is 10-20 minutes and can be administered at any time on specified study visits.

#### **8.6.5 Parkinson's Non-Motor Symptom Questionnaire (NMSQuest)**

The NMSQuest is a validated 30 question scale designed to detect the non-motor features of Parkinson's disease. (Chaudhuri et al., 2006) The duration of the scale is 5-10 minutes and can be administered at any time on specified study visits.

#### **8.6.6 Electrocardiogram (ECG) Procedure**

A standard 12-lead ECG single read will be conducted at selected study visits. Prior to the assessment the participant should be rested in a supine position for 10 minutes.

If any ECG finding that is judged by the site investigator as a clinically significant change (worsening) compared with Visit 3, Day 1 (baseline, pre-dose) value will be considered an

adverse event, recorded on the source documentation and the CRF. If results are abnormal repeat testing may be performed and checked by the CI/PI or PI-delegated clinician.

### 8.6.7 Lumbar Puncture (LP)

The LP procedure will be undertaken using aseptic technique as part of a morning assessment. The CSF collection should be performed using a small calibre atraumatic needle (e.g. 22 or 24 gauge Sprotte needle). During the procedure local anaesthetic will be used. The CSF will be collected using the traditional gravity drip method. Up to 20 mL (5-6 teaspoons) of CSF will be taken for analysis and storage, please refer to the latest laboratory manual for sample collection, processing transport and analysis.

After the LP procedure the participant must lay down (rest) for a minimum of 1 hour. The participant will be contacted by the research team within 5 days of the procedure to assess any adverse events or concomitant medication and advise the participant accordingly as part of the telephone visit. Participants will be advised to remain well hydrated, and to perform light activities for the next 48 hours.

#### 8.6.7.1 Lumbar Puncture Restrictions

There are no restrictions to the study except the use of warfarin and other anticoagulants as described in the inclusion criteria and the requirements for a fasting CSF samples. Each participant must provide a fasting CSF sample for each LP procedure at the following visits: screening visit 2, visit 6 (day 186) and an optional LP at visit 7 (day 279). Participants are required to fast for a minimum of 4 hours before the LP procedure (no food except water).

### 8.7 CSF Biomarkers Analysis

CSF samples will be collected and analysed, please refer to the latest version of the AiM-PD laboratory manual. All sample collection, processing and analysis are within European Union.

| CSF Biomarker (Up to 20 mL)                              |                           |
|----------------------------------------------------------|---------------------------|
| ELISA (enzyme-linked immunosorbent assay) antibody panel |                           |
| α-synuclein                                              | Interleukin-8, Macrophage |
| t-tau                                                    | Inflammatory protein 1α   |
| p-tau                                                    | Monocyte chemoattractant  |
| β-amyloid                                                | protein-1 (MCP-1)         |
| Neurofilament light chain                                | TNF-α (tumour necrosis    |
| Neurogranin                                              | factor alpha)             |
| Lysosomal marker panel                                   |                           |
| Enzyme activity panel                                    |                           |
| Glucocerebrosidase (GCase)                               |                           |
| Chitotriosidase                                          |                           |
| CSF ambroxol levels                                      |                           |
| CSF Cell Count                                           |                           |
| CSF glucosylceramide                                     |                           |
| CSF glucocerebrosidase protein                           |                           |

### 8.8 Routine and Study Related Blood Collection Analysis

Blood samples will be collected and analysed, please refer to the latest version of the AiM-PD laboratory manual.

#### Blood Biomarker (From 25-80 mL per visit)\*

| ELISA antibody panel antibody panel                                                                                      |                                                                                                                                                           |
|---------------------------------------------------------------------------------------------------------------------------------|-----------------------------------------------------------------------------------------------------------------------------------------------------------|
| $\alpha$ -synuclein
t-tau
p-tau
$\beta$ -amyloid
Neurofilament light chain
Neurogranin
Lysosomal marker panel | Interleukin-8
Macrophage Inflammatory protein 1 $\alpha$
Monocyte chemoattractant protein-1 (MCP-1)
TNF- $\alpha$ (tumour necrosis factor alpha) |
| Enzyme activity panel                                                                                                    |                                                                                                                                                           |
| Glucocerebrosidase
Chitotriosidase
Lysosomal glucocerebrosidase                                                           |                                                                                                                                                           |
| Blood ambroxol levels                                                                                                    |                                                                                                                                                           |
| Routine blood panels                                                                                                     |                                                                                                                                                           |
| Haematology Panel
Biochemistry Panel
Coagulation Panel
Serum uric acid                                                 |                                                                                                                                                           |
| Serum Blood Pregnancy Test (if applicable)                                                                               |                                                                                                                                                           |
| GBA Genotyping                                                                                                           |                                                                                                                                                           |
| GBA Genetic Analysis
LRRK2 Genetic Analysis                                                                                  |                                                                                                                                                           |

\*Please refer the latest version of laboratory manual for detailed volumes of blood required for each visit.

## 8.9 Study Related Urine Collection Analysis

Pregnancy urine samples will be collected and analysed, please refer to the latest version of the AiM-PD laboratory manual.

| Urine                                                                                |
|---------------------------------------------------------------------------------------------|
| Urine pregnancy test*
*For female participants of child bearing potential, if applicable |
| Urine collection (Up to 50 mL)                                                              |

Urine samples will be stored for future proteomics, metabolomics and lipidomics studies related to the PD biomarker detection and also High Performance Liquid Chromatography (HPLC) assays to detect ambroxol levels in the urine.

## 9. Assessments and Follow Up

All participants will undertake study related procedures at specified visits, please see Appendix 1 for detailed schedule of events.

### 9.1 Screening Visit 1 (within 60 days of Day 1, pre-treatment phase)

- Informed consent
- Medical history
- Physical and neurological examinations

- Screening genotyping (*GBA* and *LRRK2*), if applicable
- Vital signs (HR, BP, RR and T)
- Height and weight (morning assessment)
- ECG
- For female participants of child bearing potential, serum pregnancy test if applicable
- Routine blood collection
- Blood collection enzyme activity & ELISA antibody panels
- Blood ambroxol collection
- Adverse event review
- Concomitant medication review

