## **9.2 Screening Visit 2 (within 60 days of Day 1, pre-treatment phase)**

- Physical and neurological examinations
- MDS-UPDRS (morning assessment)
- Screening inclusion/exclusion criteria
- Vital signs (HR, BP, RR and T)
- Weight (morning assessment)
- ECG
- For female participants of child bearing potential, urine pregnancy test if applicable
- Routine blood collection
- Lumbar puncture (up to 20 mL) (morning assessment)
- CSF collection enzyme activity & ELISA antibody panels
- CSF ambroxol collection
- Adverse events review
- Concomitant medication review

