### **9.20 Treatment Phase - Visit 6 - Day 186 (+/- 14 days)**

- Physical and neurological examinations
- MDS-UPDRS (morning assessment)
- Vital signs (HR, BP, RR and T)
- Weight (morning assessment)
- ECG
- Lumbar puncture (up to 20 mL) morning assessment
- For female participants of child bearing potential, urine pregnancy test if applicable (pre-dose)
- Routine blood collection
- Blood collection enzyme activity & ELISA antibody panels
- CSF collection enzyme activity & ELISA antibody panels
- Blood ambroxol collection
- CSF ambroxol collection
- Urine collection (morning assessment)
- Dosing on site, IMP Administration - Day 1 to Day 186 (inclusive), last day of dose
- Collecting IMP packaging
- MoCA cognitive assessment (morning assessment)
- NMSS and NMS Questionnaire
- Adverse events review
- Concomitant medication review

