| Routine bloods** b                    | X         | X   |                    |                         |      |      |                                         | X                                       |           |                                         |           |                                         |                                         |           |                |                                         |                                         |                |           |                                         | X              |                | X                        |   | X              |   |
| Blood enzyme activity & ELISA**                  | X         |     |                    |                         |      |      |                                         | X                                       |           |                                         |           |                                         |                                         |           |                |                                         |                                         |                |           |                                         | X              |                | X                        |   | X              |   |
| Blood ambroxol**                                 | X         |     |                    |                         |      |      |                                         | X                                       |           |                                         |           |                                         |                                         |           |                |                                         |                                         |                |           |                                         | X              |                | X                        |   |                |   |

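### Baseline blood GCase and biomarkers come from screening visit 1, outside the fasting and PD-medication rules that apply at day 186, so the single-arm blood change carries an avoidable risk of confounding

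*Protocol*

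**What the plan says.** Section 9.1 puts "Blood collection enzyme activity & ELISA antibody panels" at screening visit 1. Section 9.2 puts "CSF collection enzyme activity & ELISA antibody panels" at screening visit 2, where the only blood listed is "Routine blood collection". Section 9.4 (day 1) lists no blood draw. The Appendix 1 row "Blood enzyme activity & ELISA" agrees: it is marked at visit 1, blank at visit 2 and day 1, then marked at visits 4, 5, 6 and 7.

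Section 9.20 (day 186) has the enzyme and ELISA blood at the same visit as "Lumbar puncture (up to 20 mL) morning assessment".

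Two rules govern the participant's state at a visit. Section 8.6.7.1 says "Participants are required to fast for a minimum of 4 hours before the LP procedure", and the lumbar punctures are at screening visit 2, visit 6 and optionally visit 7. Section 8.6.1.1 says "On screening visit 2, visit 3 (day 1), visit 5 (day 93), visit 6 (day 186) and visit 7 (day 279), participants must refrain" from their usual PD medication until the UPDRS has been done. Screening visit 1 appears in neither list.

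Section 4.2 makes the effect of ambroxol on GCase activity in blood and in CSF a secondary objective. Sections 5.1 and 13.3 describe an open-label study of 20 participants without a comparator.

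**The concern.** The baseline value is half of every change score. In a controlled trial, a difference in sampling conditions between baseline and follow-up would affect both arms and largely cancel. Here nothing cancels it. If feeding or PD medication moves blood GCase or any of the ELISA markers, the day 186 change contains that movement together with the drug effect, and no analysis can separate the two.

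The schedule also leaves no occasion before treatment on which blood and CSF come from the same visit, although that pair exists at day 186. Neither problem can be repaired once a participant has taken the first dose.

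**Working it through.** **Sampling conditions by visit** (sections 8.6.1.1, 8.6.7.1, 9.1 to 9.22, Appendix 1)

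| Visit | Enzyme/ELISA blood | CSF | Fasting list | PD medication withheld until UPDRS |
|---|---|---|---|---|
| Screening 1 | yes | no | no | no |
| Screening 2 | no (routine only) | yes | yes | yes |
| 3 (day 1) | no | no | no | yes |
| 4 (days 9-11) | yes | no | no | no |
| 5 (day 93) | yes | no | no | yes |
| 6 (day 186) | yes | yes | yes | yes |
| 7 (day 279) | yes | optional | only with optional LP | yes |

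The baseline blood matches visit 4 on both rules and differs from visit 6 on both. Screening visit 2 matches visit 6 on both and already includes a venepuncture.

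**What 20 participants can resolve.** The protocol gives no variance and no sample size calculation (13.4), so there is no figure to reproduce and the scale has to be the SD of the within-person change. The half-width of a 95% interval for the mean change is t(0.975, n-1)/√n:

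- n = 20: 0.47 SD
- n = 10 (one GBA group): 0.72 SD

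Section 13.5 plans Bayesian credible intervals. With normal data and the usual vague prior these coincide with the t interval, so it serves as a stand-in.

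**Effect of a systematic shift (assumed sizes).** Suppose the drug does nothing and the difference in conditions shifts the change by b SD. The chance that the interval excludes zero is 1 - [F(t) - F(-t)], where F is the noncentral t distribution with n-1 degrees of freedom and noncentrality b√n.

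| Assumed shift b | n = 20 | n = 10 |
|---|---|---|
| 0 | 5% | 5% |
| 0.1 | 7% | 6% |
| 0.2 | 14% | 9% |
| 0.3 | 25% | 14% |
| 0.5 | 57% | 29% |

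**Effect of extra noise (assumed sizes).** If uncontrolled conditions at visit 1 add k times the within-person variance to the baseline, the SD of change is multiplied by √((2+k)/2) and the sample size needed for the same precision by (2+k)/2.

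- k = 0.25: SD up 6%, sample size 1.13 times
- k = 1: SD up 22%, sample size 1.5 times

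The values of b and k are illustrations. Nothing in the protocol supports one value over another, including zero.

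**The case against.** The strongest reply is that the difference in conditions is inferred from silence. The protocol does not say that visit 1 blood is taken fed or on medication; it only leaves visit 1 off two lists. Section 9.20 gives no order for blood draw, lumbar puncture, UPDRS, medication and food, so day 186 blood might be drawn after eating or after medication. Blood handling is left to a laboratory manual that is not shown (8.8), and the manual may set fasting or timing. No passage says that feeding or PD medication affects these markers. All of this stands, and it makes the point a risk and not a demonstrated bias. It does not remove the point: the protocol fixes the visit, and the manual cannot put visit 1 blood and visit 2 CSF into the same visit.

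A second reply also stands. Visit 4 is under neither rule, so simply moving the baseline to visit 2 would match day 186 and unmatch visit 4. The fix has to serve both.

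Several stronger readings are tempting, and the documents do not support them:

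- **Time of day.** A reader might infer a different clock time at visit 1. Section 9.1 already has a morning assessment there (height and weight), and no difference is documented.
- **Interval.** A reader might expect a visit 2 draw to shorten the gap to treatment. Visit 2 has the same window of 60 days before day 1. Baseline to day 186 can run from 186 - 14 - 1 = 171 days to 60 + 186 + 14 - 1 = 259 days from either visit.
- **Ambroxol.** "Blood ambroxol collection" at visit 1 is a pre-dose sample expected to be near zero, so its timing is immaterial. The on-treatment blood and CSF ambroxol samples share the day 186 visit.
- **Blood-CSF ratio.** No objective or outcome names one, so no gain in precision for such a ratio is claimed here.
- **Primary outcome.** Both mandatory CSF samples are fasting morning samples at visits with PD medication withheld until the UPDRS. The primary CSF comparison is not touched.

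**Conclusion.** The point holds as an avoidable design weakness in a secondary measure. The only baseline for blood GCase and ELISA markers comes from a visit under neither of the two rules that apply on day 186, and a visit that matches day 186 on both, with blood already being drawn, is not used. In a single-arm study any effect of those conditions is inseparable from drug effect in the day 186 blood change.

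The size and direction are unknown. A shift of 0.2 SD of change would raise false signals at n = 20 from 5% to 14%, and 0.5 SD would raise them to 57%; if the conditions have no effect on these markers, there is no bias. The conclusion assumes that the laboratory manual does not already impose matched conditions on visit 1. Even if it does, same-visit blood and CSF samples before treatment would still be missing. The text and Appendix 1 agree with each other, so this is a design choice to improve and not an inconsistency to correct.

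**What to change.** Add the blood enzyme activity and ELISA draw to section 9.2 and to the screening visit 2 column of Appendix 1. Take it with the routine bloods on the lumbar puncture morning, in the same order relative to food and PD medication as at visit 6, and write that order down for both visits. Name this sample as the baseline for the day 186 blood change.

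Keep the visit 1 sample as a second baseline for visit 4, which is under neither rule. Day 93 and day 279 blood would still be only partly matched on fasting and should be reported with that noted.

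The cost is a few extra tubes and assays per participant, an amendment to 9.2, Appendix 1 and the laboratory manual, and a larger blood volume on the lumbar puncture day. Visit 6 already combines the same draws with a lumbar puncture.
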